### Intervention Groups

#### Summary

After randomization, participants in both groups will complete an initial training session (1 hour) to introduce the intervention. The initial training session will consist of a health and exercise history assessment, tailored exercise prescription, goal setting, and software account setup, as described in the following sections. Both groups will also receive weekly videoconferencing calls (30-60 minutes) from the study team via Microsoft Teams. Weekly sessions will involve a review of training and any adverse events, progression or adaptation of the program as needed, and troubleshooting of any difficulties encountered by the participant. Participants will also have the option of scheduling additional sessions with the study team during the week if further support is needed.

#### Physical Training Group

##### Overview

Participants in the physical training group will perform 8 weeks of home-based physical exercise training as per the current standard of care for pulmonary rehabilitation [22,33]. The physical training program was developed according to established guidelines for pulmonary rehabilitation [22,33] and includes both aerobic and strength training exercises that will be individually tailored to the specific needs and physical condition of each participant. Table 1 summarizes the physical exercise training program parameters.

**Table 1 table1:** Physical exercise training parameters.

Modality and frequency	Intensity	Time	Type	Progression
Aerobic: 5 days/week	Moderate to vigorous (target Borg RPE^a^ score of 4-6/10) 60%-85% of symptom-limited maximum heart rate	30-50 minutes Either continuous or interval training	Foot peddler	Gradual progression of training duration Increase pedaling speed (revolutions/minute) or resistance Increase target heart rate or RPE score
Strength: 2 days/week	Target Borg RPE score of 4-6/10	6 exercises 1-3 sets 10-12 repetitions	Resistance band exercises: band pull-aparts, seated bicep curls, seated rowing, and seated tricep kicks Body weight exercises: chair sit-to-stand exercises and calf raises	Resistance intensity will be increased when prescribed exercises can be completed without difficulty to maintain moderate exertion Increase in resistance band tension Increase in number of sets or repetitions

^a^RPE: Rating of Perceived Exertion.

Individualized progressive exercise prescriptions will be developed by an exercise professional and supported using a web application and mobile app (Physiotec) that allows for customizable exercise prescriptions with written instructions, video tutorials, and self-reported tracking of exercise completion. The exercise program will be reviewed, revised, and progressed as appropriate based on participants’ needs during the weekly check-ins with the exercise professional. This will involve reviewing available data from Fitbit and self-report records from the participant, including pulse oximeter recordings.

Participants will be encouraged to include a warm-up and a cooldown period as part of their exercise training sessions. The warm-up will be a 5-minute routine consisting of mobility and breathing exercises to be implemented before starting physical activity. The cooldown at the end of each training session will comprise neck, shoulder, and leg stretches. See Table 2 for examples of warm-up and cooldown exercises.

**Table 2 table2:** Summary of warm-up and cooldown exercises.

Exercise		Intensity	Time	Type
**Warm-up (5 minutes)**				
	Breathing	As tolerated Gentle breathing exercises	Approximately 3 minutes	Pursed-lip breathing
	Mobility	Gentle mobility exercises as tolerated by the participants’ range of motion while combining with the rhythm of breathing	5 exercises 1 set of 10 repetitions	Neck mobility (chin tuck and head to the sides) Shoulder circles Arms reach up and reach down (touch ankles) Knee extension and flexion (performed while sitting in a chair)
**Cool down (5 minutes)**				
	Stretching	Gentle stretching exercises as tolerated by the participants’ range of motion	3 exercises 1 set of 2 repetitions for each exercise Hold each exercise for 10 seconds	Chest stretching in chair Back stretching in chair Leg stretching in chair

##### Aerobic Training

Aerobic training will consist of using a foot peddler (VANGONA D2 pedal exerciser) provided by the research team (Table 1). Participants will be asked to perform aerobic training 5 times per week for a minimum of 30 minutes (up to 50 minutes) at a moderate to vigorous intensity (level 4-6 out of 10 on the Borg Rating of Perceived Exertion [RPE] Scale). Aerobic exercise may be performed in intervals (eg, 5 minutes of pedaling and 2 minutes of rest) or completed in shorter bouts throughout the day if participants cannot tolerate 30 minutes continuously. Exercise duration and intensity will be adapted to the participants’ level of dyspnea and fatigue. Aerobic training will progress under the guidance of the exercise professional by increasing duration, cycling speed, and resistance.

##### Strength Training

Strength training will be performed 2 times per week using resistance bands (provided by the research team), the participants’ own body weight, and household items (eg, chairs). Participants will be prescribed 1 to 3 sets of 10 to 12 repetitions for 6 strength exercises targeting large muscle groups such as the chest, back, arms, shoulders, and legs. Exercises may include band pull-aparts, seated rowing, bicep curls, triceps extensions, sit-to-stand exercises, and calf raises. Specific exercises and the number of sets and repetitions will be tailored to suit the individual needs of each participant, with a target intensity level of 4 to 6 on the Borg RPE Scale. Strength training will be performed under the guidance of the exercise professional by increasing the number of sets or repetitions or by increasing the tension in the resistance bands.

##### Safety Precautions for Remote Training

Participants will be given a personalized exercise program supervised by a qualified exercise professional. The exercise professional will review important considerations for home exercise, such as maintaining an open training environment free from tripping hazards (eg, rugs, clutter, and pets), the suitability of exercise equipment setup, and appropriate exercise attire (eg, footwear). Before beginning the remote exercise sessions, the exercise professional will perform a safety check to determine the appropriateness of proceeding with testing or training. The safety check will involve an objective assessment of oxygen saturation, heart rate, and blood pressure (if available) and a subjective assessment of self-reported symptoms (eg, breathlessness, dizziness, and chest pain). The research team will also collect participants’ home addresses, telephone numbers, and emergency contact information to be used in the event of a medical emergency during internet-based interactions.

Participants will be instructed to monitor their oxygen saturation (pulse oximeter), heart rate (pulse oximeter or Fitbit), and subjective level of exertion (Borg RPE Scale) and breathlessness (Borg Dyspnea Scale) while exercising using printed scales. They will be advised to lower their intensity level (ie, decrease cycling speed or resistance) if they reach a score of ≥7 on the Borg Dyspnea or RPE Scales, if their oxygen saturation drops to <85%, or if they experience any other symptoms (eg, light-headedness). They will be asked to track any adverse events using the training diary and encouraged to contact a member of the research team immediately upon noticing any adverse events. If participants experience chest pain or discomfort (uncomfortable feeling of pressure, pain, squeezing, or heaviness in the chest spreading to the shoulder, arms, neck, and back), they will be instructed to immediately stop exercising, rest, and seek emergency medical assistance if the symptoms persist beyond 5 minutes. The training program will be monitored by the exercise professional via weekly internet-based appointments involving a review of physiological exercise parameters (heart rate and oxygen saturation) from the Fitbit data and participant self-reported records. Participants will also be able to contact the exercise professional and study team at any time if questions or concerns arise.

If a participant communicates a medically concerning adverse event or contraindication to exercise (eg, cardiovascular event), the program will be suspended until medical clearance to resume the exercise program is obtained from the participant’s physician and approved by the principal investigator. Participants who experience a COPD exacerbation during the study will be instructed to temporarily discontinue their training program. They will be reassessed by the principal investigator and exercise professional within 2 weeks for their ability to resume the study.

#### Cognitive-Physical Training Group

##### Overview

Participants in the cognitive-physical training group will perform 8 weeks of home-based web-based cognitive training in addition to physical exercise training.

##### Physical Exercise Training

Physical training, including aerobic and strength exercises identical to those in the physical training group, will be performed a minimum of 5 days per week, as described previously.

##### Cognitive Training

Cognitive training will be performed using the web-based BrainHQ training platform (Posit Science Corporation) [34]. Participants will be instructed to train 5 days per week with a target of 24 levels per session (approximately 60 minutes). Cognitive training may be completed on a desktop computer, laptop, or tablet. A tablet device will be provided to any participants without access to a personal device for training. A customized training focus has been designed for this study based on areas of cognition known to be affected by COPD: attention, memory, speed of processing, and executive function [6-8]. These cognitive domains will be targeted using the following BrainHQ exercises: Double Decision, Hawk Eye, Visual Sweeps, Eye for Detail, Mind Bender, and Target Tracker [35,36]. The BrainHQ platform is designed to have training difficulty continuously adjusted to be performed “at threshold” of 70% to 80% accuracy, meaning that exercises become easier or more difficult based on the individual’s performance. All participants in the cognitive-physical training group will have a similar training session initially, but training parameters will become more individualized as users progress and the algorithm considers their individual performance history. Previous research indicates that the proposed training schedule (8 weeks, 40 hours total) is sufficient to elicit cognitive improvements [35,37,38].

### Data Collection

#### Primary Outcomes

##### Overview

The primary outcomes for this study include the following indicators of intervention feasibility: recruitment rate, retention, adherence, safety, and satisfaction. See Table 3 for an overview of the feasibility outcomes.

**Table 3 table3:** Feasibility outcome measures.

Feasibility outcome	Assessment measure	Success criteria	Time point
Recruitment	Number of consented participants relative to the total number of eligible patients approached for consent	Recruitment rate of ≥30%	During study period
Retention	Number of participants who complete the final study assessment relative to the total number of participants enrolled and randomized	Retention rate of ≥80%	During study period
Adherence	Percentage of completion of physical and cognitive training intervention components according to training logs and BrainHQ records	Intervention adherence of ≥75%	During study period
Safety	Adverse events reported via exercise training logs and weekly check-in sessions	No study-related adverse events	During study period
Satisfaction	Participant satisfaction survey	≥80% reporting above-average or excellent satisfaction on a Likert scale	Weeks 1, 4, and 8

##### Recruitment

The recruitment rate will be defined as the percentage of consented patients relative to the total number of eligible patients who agreed to be approached by the study team for participation. Reasons for study participation and nonparticipation will also be collected. A recruitment rate of ≥30% has been established as our criterion to inform feasibility for a future study and help with modifications to recruitment for future studies.

##### Retention

Retention for the whole study and per group will be defined by the number of participants who complete the final study assessment compared with the number of participants enrolled and randomized. A retention rate of ≥80% (in each group) has been established as our criterion to determine feasibility for a future study.

##### Adherence

Adherence to the prescribed physical training and cognitive-physical training programs will be assessed via daily exercise training logs, the number of training levels completed in BrainHQ (displayed on a secure cloud-based group portal accessible by the study team), and weekly communications with participants. Adherence to the physical exercise training intervention will be expressed as the percentage of physical training days completed out of the total number of training days prescribed. Adherence to the cognitive training intervention will be expressed as (1) the number of cognitive training days completed out of the number of cognitive training days prescribed and (2) the number of cognitive training levels completed out of the total number of levels prescribed using the BrainHQ platform. Adherence to the interventions of ≥75% (ie, combination of physical training logs and cognitive training platform) is our criterion to determine feasibility for a future study.

##### Safety

Intervention safety will be monitored based on the occurrence and severity of adverse events. Participants will be instructed to log and report any side effects or adverse events during the intervention (ie, falls, injuries, and respiratory symptom worsening). Adverse events will also be reviewed by the exercise professional during weekly sessions.

##### Satisfaction

Participant satisfaction with the cognitive-physical training and physical training programs will be assessed at weeks 1, 4, and 8 using a Participant Evaluation Questionnaire developed for this study involving multiple-choice and open-ended questions. The results will be reviewed and analyzed by the study team at the end of the trial to determine overall satisfaction and any modifications required for future trials.

#### Secondary Outcomes

##### Overview

Effect size estimates will be evaluated using secondary outcome measures of physical and cognitive function, dual task performance, ADLs, and HRQL, as described in further detail in the following sections. These measures will be assessed at baseline and at 4 and 8 weeks after starting the intervention. See Table 4 for a summary of secondary outcome measures.

**Table 4 table4:** Secondary outcome measures by time point.

Outcome		Assessment measure	Time points
**Characterization measures**			
	Sociodemographic information	Sociodemographic questionnaire	Baseline
	Cognitive screening	Montreal Cognitive Assessment Test	Baseline
	Disease impact	COPD^a^ Assessment Test	Baseline, week 4, and week 8
	Clinical characteristics	Medical chart review	During study period
**Physical function**			
	Lower-body strength	1-Minute Sit-to-Stand Test	Baseline, week 4, and week 8
	Lower-body function	Short Physical Performance Battery	Baseline, week 4, and week 8
	Aerobic endurance	Foot peddler endurance test	Baseline, week 4, and week 8
	Cognitive performance	BrainHQ assessment	Baseline, week 4, and week 8
	Dual-tasking performance	Foot peddler dual task test	Baseline, week 4, and week 8
**Self-reported outcomes**			
	Dyspnea	MRC^b^ Dyspnea Scale 18-item qualitative dyspnea scale Borg Dyspnea and RPE^c^ Scales	Baseline, week 4, and week 8
	Activities of daily living	The London Chest Activity of Daily Living scale	Baseline, week 4, and week 8
	Health-related quality of life	St. George’s Respiratory Questionnaire	Baseline, week 4, and week 8
	Mood	Depression, Anxiety, and Stress Scale (21 items)	Baseline, week 4, and week 8
	Exercise self-efficacy	Exercise Self-Regulatory Efficacy Scale	Baseline, week 4, and week 8
**Physical activity**			
	Physical activity habits	International Physical Activity Questionnaire–Short Form	Baseline
	Physical activity behaviors	Fitbit activity tracker	During study period
	Health care use	Medical chart review Self-reported	During study period and 1 year before study enrollment

^a^COPD: chronic obstructive pulmonary disease.

^b^MRC: Medical Research Council.

^c^RPE: Rating of Perceived Exertion.

##### Characterization Measures

###### Sociodemographic Information

Age, sex, ethnicity, employment status, educational level, and smoking history will be collected via chart review and self-report to characterize the sample and interpret findings from the cognitive assessments.

###### Montreal Cognitive Assessment

The Montreal Cognitive Assessment (MoCA) [39] is a 30-point screening test for mild cognitive impairment that has been previously applied in patients with COPD [12,40]. The MoCA specifically assesses short-term memory, visuospatial abilities, executive function, attention, concentration, working memory, language, and orientation to time and place. The MoCA will be administered only at the baseline assessment to help characterize the study population.

###### COPD Assessment Test

The COPD Assessment Test [41] is a short questionnaire for assessing and monitoring the impact of COPD. The COPD Assessment Test consists of 8 items that assess cough, the production of phlegm, chest tightness, breathlessness, activity limitation, confidence, sleep, and energy. Each item is rated on a 6-point scale, and the overall score ranges from 0 to 40, with a higher score indicating greater disease impact.

###### Clinical Characteristics

Clinical characteristics, including FEV_1_; medications (eg, inhaled medications, opioids, and prednisone); baseline 6-minute walk distance; Body Mass, Obstruction, Dyspnea, and Exercise index; and exacerbation history, will be ascertained from chart review up to 1 year before study enrollment. We will also capture anthropometric measures and BMI from pulmonary function tests if available from routine clinical evaluations. Comorbidities in our study participants will be assessed using the Charlson Comorbidity Index and through chart review using a comprehensive comorbidity questionnaire previously applied by our group [42].

##### Physical Function

###### Lower-Body Strength

The 1-Minute Sit-to-Stand Test [43] will be used to evaluate lower-body strength. This test involves participants completing as many sit-to-stand rises from a chair as possible in 1 minute. Participants will be instructed to stand fully upright and then sit down again immediately without delay, with arms crossed at the chest to avoid the use of the arms to rise from the chair. The research team will guide participants in selecting an appropriate chair (approximate height of 46 cm) with a flat, noncushioned bottom and no armrests. Participants will be prompted to report their Borg Dyspnea and Borg Leg RPE scores before and after the test.

###### Lower-Body Function

The Short Physical Performance Battery [44] will be used to assess lower-extremity performance, including balance (ability to stand with feet side by side, semitandem, and tandem), gait (usual-paced walking speed over 4 meters), and chair stand (time to rise from a chair 5 times). The Short Physical Performance Battery score is a summation of the scores on the 3 tests, each scored from 0 to 4, with a maximal cumulative score of 12.

###### Aerobic Endurance

Aerobic endurance will be measured using a foot peddler test developed by our research group for this study. Participants will pedal for as long as they can up to 15 minutes at a set speed of 50 revolutions per minute and a resistance setting that allows them to carry on a conversation (approximately 3-4 on the Borg RPE Scale). This intensity level is intended to be challenging but not exhausting. The primary endurance measure will be the number of minutes of testing completed. The reason for test termination will also be recorded. Oxygen saturation, qualitative dyspnea descriptors, Borg Dyspnea score, and Borg Leg RPE score will be measured before and after endurance testing. The complete aerobic endurance testing protocol is described in Textbox 1.

Aerobic endurance foot peddler testing protocol.

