**Test period**
Participants will continue pedaling at a set speed of 50 revolutions/minute and a resistance setting that allows them to carry on a conversation (approximately 3-4 on the Borg Rating of Perceived Exertion Scale) for as long as they can up to a maximum of 15 minutes. Participants will be prompted every few minutes to monitor their heart rate and oxygen saturation using an oximeter and their Borg Dyspnea score. The test will be stopped based on any of the following stopping criteria:15 minutes have been completed.Oxygen saturation drops to <85%.Self-reported Borg Dyspnea score is >7.The activity becomes unbearable (eg, severe leg pain or the participant is too tired to continue).Heart rate reaches 85% of age-predicted maximum (calculated as 220 beats/minute–age).Participant is unable to maintain a speed of 50 revolutions/minute.The research team member decides to stop the test because of apparent breathlessness or discomfort of the participant.

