##### Dual Task Performance

Dual task performance will be evaluated through a dual task test on the foot peddler, as previously undertaken in other populations [46,47]. Participants will complete a motor, cognitive, and combined dual task (all of 1-minute duration) in random order: (1) the *cognitive task* involves spelling 5-letter words backward from a list of 100 words provided verbally (homonyms excluded), (2) the *motor task* involves pedaling on the foot peddler at a set speed of 50 revolutions per minute and a self-selected resistance corresponding to a moderate-intensity level allowing participants to hold a conversation (approximately level 4 on the Borg RPE Scale), and (3) the *dual task* involves spelling and pedaling at the same time. Participants will be instructed to prioritize both tasks equally. Spelling tasks (single and dual tasks) will be audio recorded using a Dictaphone to allow for precise scoring. The number of words correctly spelled backward and the distance covered while pedaling will be compared between the single and dual task conditions to calculate a dual task cost score for both the cognitive and physical performance tasks.

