### Strengths

There are several strengths to this study. The physical training program and assessments were specifically designed to support feasibility and safety in the home environment. All participants will be provided with exercise training equipment (foot peddler, resistance bands, Fitbit, and pulse oximeter), which will improve safety and accessibility and standardize physical training and assessments. This study is novel as it provides a new approach to remote assessments of aerobic endurance (ie, foot peddler), functional outcomes, and cognitive assessment and training as part of a home-based pulmonary rehabilitation program for patients with COPD [27]. Our protocol may optimize not only accessibility but also outcomes in home-based pulmonary rehabilitation programs. The use of commercially available software programs (Fitbit, Physiotec, and BrainHQ) supports the future clinical translation of this work as these and other similar programs may be used by clinicians and patients looking to integrate cognitive-physical training into pulmonary rehabilitation programs. Furthermore, the chosen cognitive training platform (BrainHQ) has the largest evidence base and, to our knowledge, is the only brain training program that meets all the National Academy of Medicine criteria for cognitive training [29,30]. Our specific cognitive training protocol was designed in consultation with neuropsychology and cognitive science experts to specifically target common areas of deficit among individuals with COPD.

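### The endurance test defines resistance only by perceived exertion and states no record of the setting, so minutes completed may not be comparable between visits

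*Protocol article*

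**What the plan says.** The Aerobic Endurance section of the protocol article describes the test as follows: "Participants will pedal for as long as they can up to 15 minutes at a set speed of 50 revolutions per minute". Resistance is "a resistance setting that allows them to carry on a conversation (approximately 3-4 on the Borg RPE Scale". On scoring: "The primary endurance measure will be the number of minutes of testing completed".

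The section then says "The complete aerobic endurance testing protocol is described in Textbox 1". The Test period part of Textbox 1 repeats the same rule: "a resistance setting that allows them to carry on a conversation (approximately 3-4 on the Borg Rating of Perceived Exertion Scale) for as long as" …

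Table 4 schedules the test at baseline, week 4 and week 8. The Data Analysis section compares changes over 8 weeks, by paired t tests within groups and two-sample t tests between groups. It says the estimates will serve sample size calculations for a larger trial.

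The Dual Task Performance section also uses 50 revolutions per minute, with "a self-selected resistance corresponding to a moderate-intensity level allowing participants to hold a conversation (approximately level 4 on the Borg RPE Scale". Its words and distance "will be compared between the single and dual task conditions to calculate a dual task cost score for both the cognitive and physical performance tasks".

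**The concern.** At a fixed cadence, resistance determines the workload. An endurance time means something only relative to the load at which it was obtained. Here the load is described by how hard it feels, and the training is meant to change exactly that. Both arms train on the same pedal device, with resistance progressed over the 8 weeks (Aerobic Training; Table 1).

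If the setting that feels like 3 to 4 is found again at week 8, a fitter participant will be on a harder setting. Minutes at week 8 and minutes at baseline then come from two different tests. A real gain may show as a small gain, no change or a slight loss, and a participant who happens to choose a lighter setting appears improved. Variation in the chosen load also adds noise to the change score, and so to the standard deviation carried into the next trial's sample size. Table 4 lists no other aerobic endurance test. The problem is separate from the 15-minute cap, since it also affects someone who stops well short of it.

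**Working it through.** The plan gives no figure to reproduce: the Sample Size section says no power calculation was made for secondary outcomes. The check is a reading of the text, followed by an illustration.

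**Reading**

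1. *Rule for the load.* Both descriptions of the endurance test give the exertion target and nothing else.
2. *What is recorded.* Textbox 1 lists oxygen saturation, heart rate, dyspnea descriptors, Borg Dyspnea, Borg Leg exertion, the reason for stopping and participants' comments. The resistance setting is not listed.
3. *Carrying forward.* Nothing says the baseline setting is reused, and nothing says it is chosen again.
4. *Possible cures.* Study Timeline says equipment setup is determined at familiarization. Data Quality and Management says standard operating procedures exist for all study procedures. Neither names resistance.

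**Illustration (every input is assumed; none is in the documents)**

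Time to stopping is taken as t = W′/(P − CP), where P is the load, CP is critical power and W′ is a fixed work reserve, capped at 15 minutes. Let the baseline load be P = m·CP and the baseline time t0. After training, CP rises by a fraction g, W′ is unchanged, and the load is raised by a share s of that gain. Then

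t1 = t0·(m − 1) / [m(1 + s·g) − (1 + g)]

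Inputs: m = 1.1, 1.2, 1.4; t0 = 6, 8, 10 minutes; g = 5%, 10%. That gives 18 combinations for each s. Selected results in minutes, with change from baseline in brackets:

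| m | t0 | g | same load (s = 0) | half re-set (s = 0.5) | full re-set (s = 1) |
|---|---|---|---|---|---|
| 1.4 | 6 | 5% | 6×0.4/0.35 = 6.86 (+0.86) | 6×0.4/0.385 = 6.23 (+0.23) | 6/1.05 = 5.71 (−0.29) |
| 1.2 | 8 | 10% | 8×0.2/0.1 = 16, capped 15 (+7) | 8×0.2/0.16 = 10 (+2) | 8/1.1 = 7.27 (−0.73) |
| 1.1 | 6 | 10% | no finite time, capped 15 (+9) | 6×0.1/0.055 = 10.91 (+4.91) | 6/1.1 = 5.45 (−0.55) |
| 1.1 | 8 | 10% | no finite time, capped 15 (+7) | 8×0.1/0.055 = 14.55 (+6.55) | 8/1.1 = 7.27 (−0.73) |
| 1.1 | 10 | 10% | no finite time, capped 15 (+5) | 10×0.1/0.055 = 18.18, capped 15 (+5) | 10/1.1 = 9.09 (−0.91) |

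Over all 18 combinations the change is about +0.9 to +9 minutes at the same load, +0.2 to +6.6 with a half re-set and −0.3 to −0.9 with a full re-set.

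With a half re-set, the part of the gain hidden is (0.86 − 0.23)/0.86 = 73% in the first row, (7 − 6.55)/7 = 6% in the fourth and 0% in the fifth. With a full re-set, t1 = t0/(1 + g) whatever m is, so the whole gain disappears. If W′ also rose by g, t1 would equal t0.

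**Dual-task test**

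The score contrasts conditions within one visit. At 50 revolutions per minute for 1 minute the target is 50 revolutions at any resistance, so the motor cost depends mainly on cadence. The spelling cost compares seated spelling with spelling under load, so a load that differs between visits could alter the competing demand. That would blur change in cost; it would not remove it.

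**The case against.** **Re-selection is not stated.** A reader might infer that resistance is chosen anew at every visit and that training gains are therefore cancelled. The documents do not say so. Textbox 1 describes a single session, and in the endurance test period it does not say that the participant picks the setting. The setting might be fixed at familiarization under an operating procedure. This stands: non-comparability follows from applying the written rule at each visit and is not a documented practice. It does not dispose of the point, because the test description presented as complete neither records the load nor holds it.

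**The size depends on the inputs.** This also stands. The model applies only above critical power. The test is meant to be conversational and short of exhausting, so loads at or below critical power are plausible, and there the cap or another stopping criterion decides the time. No single percentage loss can be claimed.

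**Both arms do the same physical training.** A reader might infer that the comparison between groups is biased. Drift expected equally in both arms does not bias it. Bias needs a difference by arm in fitness gain or in load choice, which is possible because allocation is known to staff and participants (Randomization) but is not shown.

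**The dual-task test is affected equally.** A reader might infer this from the similar wording of the resistance rule. The within-visit contrast does not support it. Holding relative effort constant is also defensible there, since a fixed load becomes an easier motor task as fitness improves.

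**Standardization is claimed.** The Strengths section says the supplied equipment is something "which will improve safety and accessibility and standardize physical training and assessments". That concerns giving everyone the same devices. It neither promises a constant load nor provides one.

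**Endurance is secondary.** It is absent from the efficacy hypothesis in Study Purpose, and the primary outcomes are feasibility measures. This limits the weight of the point.

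**Conclusion.** The point holds for the endurance test. Load is defined only by perceived exertion, no record of it is stated and it does not enter the score, while the score is analysed as change. As written, the rule does not secure comparable minutes across visits. If it is applied afresh each time, a real gain can be reduced or hidden. In the assumed model the part hidden runs from none, where the cap governs, to all of it under a full re-set.

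The main damage is to within-group change and to the sensitivity and precision of the endurance estimate intended for planning the next trial. The between-group contrast is biased only under the arm differences described above. No feasibility outcome is touched. For the dual-task test, only a clarification is warranted.

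**What to change.** In the Aerobic Endurance section and Textbox 1, state that the exertion target is used once, at familiarization or baseline, to choose the resistance; that the setting is recorded; that the same setting is used at weeks 4 and 8; and that perceived exertion at that load is reported as an additional result. The existing stopping criteria stay as they are.

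In the Dual Task Performance section, state that the single and dual pedaling conditions within a visit use the same recorded resistance.

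The cost is about a sentence in each place and one field on the data form. There is one downside: a fixed load feels easier to improved participants, so more may reach 15 minutes. In the illustration, 7 of 18 combinations reach the cap at an unchanged load, against 1 of 18 with a half re-set. The number reaching the cap should therefore be reported beside the mean change.

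Recruitment began in January 2022, so some participants will already have been tested. Where their setting was noted, report it with the minutes. Where it was not, state the limitation when the endurance estimates are presented.
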